#### Sample size calculation

2.3.2

It is expected that 48% of the patients treated with alectinib in our study will be underdosed (i.e. C_min_ < 435 ng/mL at a certain timepoint) based on the dataset of Groenland et al. (13). The observed mPFS for these patients was 12.6 months (95% confidence interval (CI): 9.2 months – not yet reached), which will serve as the assumed median in the subgroup with low exposure in the fixed-dosing group (arm B). The mPFS in the patients with C_min_ ≥ 435 ng/mL had not yet been reached (95% CI: 19.8 months – not yet reached) at the time of analysis, but the HR for the group with C_min_ < 435 ng/mL versus C_min_ ≥ 435 ng/mL was estimated as 2.5 (13). We expect that TDM-guided dosing can improve PFS in 67% of patients with a low exposure, to the extent that they obtain a similar outcome as patients with C_min_ ≥ 435 ng/mL. In this group, a HR (fixed versus TDM-guided dosing) of 2.5 is assumed. In the remaining 33% of patients, TDM-guided dose increases are expected not to be feasible due to toxicity or treatment discontinuation as a consequence of progressive disease (PD), so a HR equal to one is assumed for this subgroup. Altogether, this would result in an expected HR (fixed versus TDM-guided) of 2.0. With 67 events, a power of 80% will be obtained to detect this HR of 2 using the log-rank test and assuming a two-sided significance level of 5%. This translates into an improvement in mPFS from 12.6 months without using TDM-guided dosing to 25.2 months using TDM-guided dosing. Assuming an uniform patient accrual during 48 months and 12 months follow-up after inclusion of the last patient (total study duration of 60 months), 94 patients (47 per group) with C_min _< 435 ng/mL will need to be included for the primary analysis. Since 48% of the patients in the study are expected to have C_min _< 435 ng/mL at a certain timepoint, 196 patients will need to be recruited (13). Dropouts are expected to be kept to a minimum and it does occur, it is expected to be in the first 12 weeks, when substitution is still allowed. Dropouts are therefore not taken into account.

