#### Primary outcome

2.3.3

The primary outcome, based on our aim to improve efficacy of alectinib treatment, is mPFS in the TDM-guided dosing arm for the C_min,SS _< 435 ng/mL subgroup, compared to this subgroup in the fixed dosing arm (standard care). PFS will be calculated as time from start of treatment to PD, death of any cause, whichever occurs first. Patients who do not progress, die, or are lost to follow-up, will be censored at their last available date. PD is defined according RECIST v1.1 and will be based on assessment using CT scans (thorax/abdomen) and MRI of the brain. In case of oligoprogression alectinib may be continued conform standard of care, but the date of oligoprogression (i.e. PD) will be used in PFS calculation. The CT scans will be performed every 8 weeks in the 1^st^ year and every 12 weeks from the 2^nd^ year onwards. The MRI of the brain will be performed every 16 weeks in the 1^st^ year if there is presence of asymptomatic brain metastases at screening and every 24 weeks from the 2^nd^ year onwards. If no brain metastases are found at screening, an MRI of the brain will be performed every 12 months (**Supplemental Table 1**).

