#### Secondary outcomes

2.3.4

There are ten secondary endpoints, defined as follows: 1) Feasibility and safety of TDM, measured as percentage of successful TDM interventions, in which successful is defined as target attainment with manageable toxicity; 2) ORR, defined as partial response or complete response (according to RECIST v1.1) percentage of the total treated population; 3) mOS, where OS is defined as time from randomization to death from any cause in the total population. Patients who do not die or are lost to follow-up will be censored at their last available date; 4) Intracranial PFS, defined as time from start of treatment to PD in the brain or death from any cause, whichever comes first. Patients not experiencing any of these events will be censored at their last available date; 5) Physician adherence to TDM advice, measured as the percentage of dose recommendations that are implemented by the treating physicians; 6) Patients’ medication adherence, estimated by pill counts of returned medication as well as a patient diary on drug intake; 7) Toxicity related to the plasma concentration and dose increases, defined as adverse events (AEs) in the subgroup with C_min,SS _< 435 ng/mL and all C_min,SS_ ≥ 435 ng/mL, and in patients who did and who did not receive a PK-guided dose increase; 8) QoL; this will be determined using the EORTC QLQ_LC13 as addition to the QLQ-C30 questionnaire, and the EQ-5D-5L questionnaire. 9) Cost-effectiveness, this will be determined from both a healthcare and a societal perspective. Costs associated with healthcare resource use in combination with Quality adjusted-life years will be used to determine an incremental cost-effectiveness ratio (ICER); 10) Alectinib-M4 concentrations, which will be measured in the alectinib plasma samples. For the endpoints regarding ORR, mOS, intracranial PFS, the comparison will be made between arm A and B, among patients who had a C_min,SS _< 435 ng/mL at any point during treatment. Feasibility and safety of TDM and physician adherence to TDM advice will only be evaluated in arm A. Patients medication adherence, toxicity, QoL, cost-effectiveness and alectinib-M4 concentrations will be evaluated in all patients.

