#### Exploratory endpoints

2.3.5

Some optional endpoints in the treatment of patients with ALK+ NSCLC are defined: 1) Predictive value of response to treatment (i.e. PFS) by next-generation sequencing (NGS) using AVENIO ctDNA test, with emphasis on acquired resistance mechanisms by the following subgroup of response: a) ctDNA profiles associated with primary resistance PD within 6 months); b) ctDNA profiles associated with acquired resistance (PD 6-24 months); c) ctDNA profiles associated with continuing response of 2 years and more; 2) Concordance of molecular profile between tumor biopsy NGS and ctDNA at baseline. As well as at PD, after performing a re-biopsy as standard of care; 3) Correlation with average daily exposure and reduction in ctDNA levels. To obtain DNA from cell free plasma, blood will be withdrawn at baseline in three Streck^®^ tubes (Streck Inc, Omaha, NE, USA) and one EDTA tube (Vacutainer) to process the buffy coat (consisting of peripheral blood mononuclear cells), to identify tumor-specific mutations using NGS analysis and exclude variants associated with germ-line, clonal hematopoiesis and technical artefacts. Each subsequent cycle, two Streck tubes will be collected. CtDNA will be analyzed using the Avenio ctDNA Expanded covering 77 clinical-relevant markers (19). There is ample experience using this Avenio ctDNA Expanded Kit of large plasma samples (20, 21).

Furthermore, additional data regarding the effects of alectinib on weight gain will be collected. These exploratory endpoints are defined as follows: 4) Parameters such as body weight, body surface area and smoking; 5) Changes in body composition measured on CT-thorax/abdomen, including subcutaneous and visceral adipose tissue measurements, using specialized software; 6) Measurements of appetite and satiety hormones and their relationship to alectinib therapy related weight gain.

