### Data analysis

2.4

Survival endpoints will be analyzed using Kaplan-Meier curves and differences between groups will be tested using the stratified log rank test. The HR and its corresponding 95% CI from a stratified Cox model will be estimated. The median survival will be presented by arm along with 95% confidence intervals using the Brookmeyer and Crowley method. A p-value < 0.05 will be deemed statistically significant.

The effect of biomarkers in the secondary and exploratory study parameters (such as sequencing profile by AVENIO of biopsy) will be explored by correlating the changes in a marker to any outcome (such as OS). This will be performed by crosstabs, t-tests, Mann-Whitney U tests, and Spearman’s rank correlations, depending on the distribution of the data.

ORR will be calculated by arm with exact 95% CI. For comparing response rates in the two-treatment arms accounting for randomization stratification factors, the Cochran-Mantel-Haenszel test will be used at a two-sided 5% level of significance.

For treatment-emergent AEs (i.e., those starting or worsening during the period on treatment) summary tables will be provided by treatment group. Worst-grade AEs will be summarized by system organ class and preferred term, severity (by CTCAE v5.0 criteria) and relation to study treatment. Serious adverse events will be listed. Statistical analyses will be specified in the Statistical Analysis Plan.

Comparative cost-effectiveness analysis will be performed using a health-state transition model, to compare costs and effectiveness between the group treated with TDM-guided dosing and the fixed dosing group. The comparative cost-effectiveness analysis will be performed from both a healthcare and societal perspective, with a lifetime horizon, according to the Dutch guidelines for cost-effectiveness analyses (22).

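### The methods named for relating marker changes to OS ignore censoring, which dilutes associations and costs power; log-rank or Cox should be named for censored outcomes

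*Protocol article*

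**What the plan says.** Section 2.4 (Data analysis) of the protocol article has a paragraph on biomarkers among the secondary and exploratory parameters. It describes their analysis thus: "explored by correlating the changes in a marker to any outcome (such as OS). This will be performed by crosstabs, t-tests, Mann-Whitney U tests". The sentence closes with a fourth method and the rule for choosing among the four: "and Spearman’s rank correlations, depending on the distribution of the data". OS is the article's own example of an outcome, and the shape of the distribution is the only stated basis for choosing a method.

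The opening paragraph of the same section takes a different line: "Survival endpoints will be analyzed using Kaplan-Meier curves and differences between groups will be tested using the stratified log rank test", with hazard ratios from a stratified Cox model.

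Both time-to-event outcomes are defined with censoring. For OS (section 2.3.4): "Patients who do not die or are lost to follow-up will be censored at their last available date". For PFS (section 2.3.3): "Patients who do not progress, die, or are lost to follow-up, will be censored at their last available date". Follow-up differs by design (section 2.3.2): "Assuming an uniform patient accrual during 48 months and 12 months follow-up after inclusion of the last patient".

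Section 2.3.5 makes PFS the outcome of the first ctDNA endpoint, "Predictive value of response to treatment (i.e. PFS) by next-generation sequencing (NGS) using AVENIO ctDNA test", but sorts it into three classes: progression within 6 months, progression at 6 to 24 months, and "ctDNA profiles associated with continuing response of 2 years and more".

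**The concern.** A t-test, Mann-Whitney test or Spearman correlation on observed survival time treats a patient censored alive at 13 months as if the survival time were 13 months, or else drops that patient. A crosstab of dead against alive ignores that one patient was watched for 12 months and another for 60. Choosing among the four by distribution can never lead to a method that accounts for this.

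At stake is the information in the marker data. The Discussion presents prospective ctDNA data in ALK-positive disease as something the field lacks. A real association could be missed or reported as weaker than it is. If a marker happened to vary with enrolment date, an association could also appear where none exists.

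**Working it through.** **Inputs from the article.** Uniform accrual over 48 months plus 12 months, so administrative follow-up is uniform from 12 to 60 months; N = 196; two-sided 5%; PFS medians of 12.6 and 25.2 months in the low-exposure subgroup (all section 2.3.2). The Introduction reports that median OS on alectinib was not reached at a median follow-up of 48.2 months.

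**Assumptions.** OS median 48, 60 or 80 months; exponential times; standard normal marker; hazard ratio 1.5 per SD; marker available in all 196 patients; no loss to follow-up before the data cut.

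**1. The plan's own figures.** Schoenfeld events for a hazard ratio of 2: 4 × (1.960 + 0.842)² / (ln 2)² = 65.3, so 66; with 67 events power is 0.81. With λ = ln 2 / median, P(event) = 1 − (e^(−12λ) − e^(−60λ)) / (48λ). This gives 0.818 and 0.601 for the two PFS medians, mean 0.7096. Then 67 / 0.7096 = 94.4 patients and 94 / 0.48 = 195.8, so 196. The plan's numbers reproduce, and the same accrual model is used below.

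**2. Share of times censored**, (e^(−12λ) − e^(−60λ)) / (48λ):
- OS median 48: (0.8409 − 0.4204) / 0.6931 = 61%
- OS median 60: (0.8706 − 0.5000) / 0.5545 = 67%
- OS median 80: (0.9013 − 0.5946) / 0.4159 = 74%
- PFS: 18% (median 12.6) and 40% (median 25.2)

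**3. How far observed time reflects follow-up.** By simulation, the rank correlation of observed time with available follow-up is 0.59 and 0.67 for OS (medians 60 and 80), but only 0.10 and 0.30 for PFS (medians 12.6 and 25.2).

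**4. Power, marker unrelated to enrolment date** (simulation, 3,000 trials per scenario). Spearman uses the continuous marker, the other tests a median split.

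| Outcome (median, months) | Log-rank | Mann-Whitney | t-test | Spearman | Crosstab of event yes/no |
|---|---|---|---|---|---|
| OS (60) | 0.73 | 0.43 | 0.43 | 0.60 | 0.70 |
| OS (80) | 0.62 | 0.30 | 0.31 | 0.43 | 0.59 |
| PFS (25.2) | 0.92 | 0.82 | 0.82 | 0.94 | 0.85 |
| PFS (12.6) | 0.97 | 0.93 | 0.95 | 0.99 | 0.84 |

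A separate simulation over OS medians of 48 to 80 months gave 0.55 down to 0.31 for Mann-Whitney and 0.79 down to 0.64 for log-rank, which agrees within simulation error. For OS, the rank correlation of marker with time falls from −0.32 without censoring to −0.16 and −0.13 (medians 60 and 80). For PFS it falls only to −0.29 and −0.25 (medians 12.6 and 25.2).

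Rough check of the log-rank figure at OS median 60: the two halves of a normal marker differ by 1.596 SD, so the log hazard ratio is about 1.596 × ln 1.5 = 0.647. Deaths are 196 × (1 − 0.657) = 67. Then √67 / 2 × 0.647 − 1.960 = 0.69, a power of about 0.75, close to 0.73.

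**5. Type I error, marker with no true effect.** Unrelated to enrolment date: 0.04 to 0.06 for all the listed methods. With an assumed correlation of 0.3 with enrolment date:

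| Outcome (median, months) | Log-rank | Mann-Whitney | t-test | Spearman | Crosstab |
|---|---|---|---|---|---|
| OS (60) | 0.05 | 0.49 | 0.50 | 0.66 | 0.11 |
| OS (80) | 0.06 | 0.60 | 0.59 | 0.77 | 0.10 |
| PFS (25.2) | 0.04 | 0.18 | 0.23 | 0.24 | 0.17 |
| PFS (12.6) | 0.06 | 0.07 | 0.09 | 0.08 | 0.20 |

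At an OS median of 48 months, the lowest of the three time-based rates is about 0.40 (Mann-Whitney).

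**6. The ctDNA classes.** With at least 12 months of follow-up, progression within 6 months is known for everyone except early losses. Membership of the 2-year class is unknown for patients event-free with under 24 months of follow-up: (e^(−12λ) − e^(−24λ)) / (48λ) = (0.5168 − 0.2671) / 2.641 = 9% for a PFS median of 12.6, and (0.7189 − 0.5168) / 1.320 = 15% for 25.2.

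**The case against.** The strongest reply has four parts.

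First, the opening sentence of section 2.4 assigns log-rank tests to survival endpoints without limiting them to the randomised arms, so comparisons of OS between marker groups could fall under it. That is a possible reading. However, the biomarker paragraph names OS and then lists its own methods, so at the least the two statements need reconciling.

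Second, the article says details will follow in a statistical analysis plan, which is not shown. That would excuse silence. Here unsuitable methods are named, so a plan that follows the article takes over the problem and one that corrects it departs from the article.

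Third, the analyses are described as exploring, the ctDNA endpoints are optional, and the Discussion says each exploratory outcome needs separate consent. This stands. It limits the weight of the point, and it makes 196 patients an upper bound.

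Fourth, not every listed method fails equally. A crosstab of dead against alive loses little power for OS (0.70 against 0.73), and a crosstab of progression within 6 months is largely valid. This stands too.

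Two stronger readings are tempting. A reader might infer that the results would follow enrolment date instead of prognosis. The documents do not support this: with a marker unrelated to enrolment, error is nominal and the weakened association still reflects prognosis. Section 2.3 says foreign sites join later, but nothing says marker values shift with site or time, and a stable site or assay shift would partly cancel in a within-patient change. A reader might also infer that using a change must build in guaranteed survival time. If the change is taken at one common sample, all analysed patients share the same guaranteed time and ranks are unaffected; bias needs sampling times that differ between patients, which the article does not establish.

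**Conclusion.** The point holds in a limited form. For OS, the article names methods that do not account for censoring, although about 60-74% of the times would be censored. The consequence to expect is dilution: Mann-Whitney power of about 31-55% where the log-rank test has 64-79%. This rests on an assumed OS median of 48-80 months, exponential times, a hazard ratio of 1.5 per SD and markers in all 196 patients.

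Inflated type I error is conditional. It reaches about 40-77% for OS with Spearman, Mann-Whitney or t-test only under an assumed 0.3 correlation with enrolment date. PFS suffers much less, apart from the 9-15% of patients who cannot be placed relative to the 2-year class. The primary and secondary arm comparisons are unaffected. The correction should be made before analysis, but it does not bear on the trial's main conclusion.

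**What to change.** In section 2.4, or in the analysis plan with a note that it supersedes the article, state:

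- Associations of markers with OS, PFS and intracranial PFS are assessed by log-rank tests or Cox models, stratified as for the survival endpoints where numbers allow.
- Baseline markers enter as fixed covariates. On-treatment changes are analysed from a landmark at a common sampling time, or as time-dependent covariates.
- Crosstabs, t-tests, Mann-Whitney tests and Spearman correlations are kept for outcomes without censoring, such as response, concentrations and body composition.
- For the ctDNA classes, how patients event-free with under 24 months of follow-up are handled.

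The cost is one paragraph; data and software stay the same. The landmark analysis drops patients with an event or censoring before the landmark. How many depends on the sample chosen, so an early common sample loses fewer.

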#### Safety assessments

2.5.2

The AEs will be assessed every visit and continuously during the study as reported by the patient in between visits. The AEs will be recorded in the electronic Case Report Forms (eCRF) according to the CTCAE version 5.0.

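### The by-arm adverse-event tables count only time on treatment, so if TDM prolongs PFS as assumed they tilt modestly against the TDM arm

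*Protocol article*

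**What the plan says.** Protocol article, section 2.4 (Data analysis), sets the window and the layout: "For treatment-emergent AEs (i.e., those starting or worsening during the period on treatment) summary tables will be provided by treatment group". It continues: "Worst-grade AEs will be summarized by system organ class and preferred term, severity (by CTCAE v5.0 criteria) and relation to study treatment". Serious AEs are listed, with no on-treatment limit attached to that listing. The paragraph then closes: "Statistical analyses will be specified in the Statistical Analysis Plan".

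Section 2.3.4 (Secondary outcomes) gives the population: "Patients medication adherence, toxicity, QoL, cost-effectiveness and alectinib-M4 concentrations will be evaluated in all patients". The toxicity endpoint there is contrasted by exposure (below 435 ng/mL versus at or above it) and by whether a PK-guided dose increase was given. Feasibility and safety of TDM is a separate endpoint, evaluated in arm A only.

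Section 2.5.2 (Safety assessments) does not tie AE collection to treatment: "The AEs will be assessed every visit and continuously during the study as reported by the patient in between visits".

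Section 2.3.2 (Sample size calculation) states the expected effect in low-exposure patients: "This translates into an improvement in mPFS from 12.6 months without using TDM-guided dosing to 25.2 months using TDM-guided dosing".

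**The concern.** A worst grade recorded over an open-ended window can only stay the same or rise as the window lengthens. Here the window is time on treatment, and the trial hopes to lengthen it in one arm only. If the primary hypothesis is true, arm A will record more AEs and higher worst grades even when the AE rate per month is the same in both arms. Apparent toxicity is then partly a by-product of efficacy, and the by-arm table alone cannot separate the effect of a higher dose from that of a longer stay on treatment. This matters because some arm A patients receive doses above the standard one, so readers will look to these tables for harm. The Discussion itself says that long-term low-grade toxicity is gaining importance, and late toxicity is the kind most affected.

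A second, smaller issue is that the definition names no period after the last dose. Taken literally, an AE that leads to stopping and then worsens is tabulated at its on-treatment grade. Section 2.2.1 gives a half-life of 32 hours, so drug is still present for some days (5 × 32 / 24 = 6.7 days for five half-lives).

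**Working it through.** **Inputs from the article.** Median PFS with low exposure is 12.6 months (arm B) and 25.2 months (arm A). The low-exposure share is 48%. The HR for low versus adequate exposure is 2.5, which gives 12.6 × 2.5 = 31.5 months for adequate exposure, taken as equal in both arms. Accrual is uniform over 48 months, with 12 months of further follow-up and no dropout.

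**Assumptions added here.** PFS is exponential. Time on treatment is PFS truncated at the data cut. The rate h of a first AE is constant and equal in both arms, from 0.01 to 0.10 per month.

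**Step 1: reproduce the plan.** Schoenfeld's formula for HR 2, two-sided 5% and 80% power gives 65.3, rounded up to 66 events; the plan states 67, at which power is 81%. With λ = ln 2 / median, the event probability is 1 − (e^(−12λ) − e^(−60λ)) / (48λ), which is 0.818 in arm B and 0.601 in arm A. So 47 × (0.818 + 0.601) = 66.7 events, and 94 / 0.48 = 195.8, or 196 patients. The exponential model therefore matches the plan's own figures.

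**Step 2: mean time on treatment.** This equals the event probability divided by λ.
- Low exposure: 14.9 months (B) and 21.8 months (A), ratio 1.47.
- Adequate exposure: 23.9 months in both arms.
- Whole arm B: 0.48 × 14.87 + 0.52 × 23.89 = 19.6 months.
- Whole arm A: 0.48 × 21.85 + 0.52 × 23.89 = 22.9 months, ratio 1.17.

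Modelling the plan's mixture directly (67% of low-exposure arm A patients at 31.5 months, 33% at 12.6) gives ratios of 1.41 and 1.15 instead.

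**Step 3: crude on-treatment incidence at equal AE rates.** For each group, incidence = h/(h+λ) × [1 − (e^(−12(h+λ)) − e^(−60(h+λ))) / (48(h+λ))]. For low exposure in arm B at h = 0.02, λ = 0.0550 and h+λ = 0.0750, so incidence is 0.2667 × (1 − 0.1098) = 0.237. Whole arms weight the low and adequate groups 48:52.

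| Rate per month | Low exposure, A vs B | Gap (points) | All patients, A vs B | Gap (points) |
|---|---|---|---|---|
| 0.01 | 18.8% vs 13.2% | 5.6 | 19.6% vs 16.9% | 2.7 |
| 0.02 | 32.7% vs 23.7% | 9.0 | 34.0% vs 29.7% | 4.3 |
| 0.05 | 57.8% vs 45.0% | 12.9 | 59.6% vs 53.4% | 6.2 |
| 0.10 | 75.7% vs 63.2% | 12.5 | 77.3% vs 71.3% | 6.0 |

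Gaps are taken from unrounded values.

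**Step 4: early AEs.** If the risk is confined to the first 3 months, incidence is h/(h+λ) × (1 − e^(−3(h+λ))). At 0.10 per month, whole arms give 25.0% (A) and 24.6% (B), so there is almost no gap.

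**Step 5: what the alternatives do.** A first-event rate per patient-month gives a ratio of 1 under equal constant rates. Cumulative incidence at 12 months with treatment stop as a competing event is h/(h+λ) × (1 − e^(−12(h+λ))). At h = 0.02 in low exposure this is 0.4210 × 0.4345 = 18.3% (A) and 0.2666 × 0.5935 = 15.8% (B). The gap shrinks from 9.0 to 2.5 points but does not vanish.

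**The case against.** The strongest reply is that this is a condensed article that defers to an analysis plan not shown. Exposure-adjusted rates and a post-dose window commonly belong there, and nothing in section 2.4 says that the crude tables will be the only safety summary. This stands as far as missing detail goes. It does not remove the point, because the article already fixes the on-treatment definition and the by-arm worst-grade layout. An analysis plan that adopts them unchanged inherits both features.

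Three stronger readings are tempting, and the article does not support them.
- A reader might infer that TDM will look more toxic because arm A stays on treatment far longer. The doubled median applies only to the low-exposure 48%, while toxicity is evaluated in all patients, where the ratio is about 1.17. The tilt also needs TDM to work, and the Discussion calls the HR of 2.0 slightly challenging. With about 98 patients per arm, the standard error of a difference such as 34.0% versus 29.7% is √(0.340 × 0.660 / 98 + 0.297 × 0.703 / 98) = 6.7 points, so the whole-arm shift is below one standard error.
- A reader might infer that these tables are the test of TDM's tolerability. Section 2.3.4 measures safety of TDM within arm A and defines the toxicity endpoint by exposure and dose increase, not by arm. No test or decision rule is attached to the by-arm tables.
- A reader might infer that worsening after the last dose is lost, and that this is the severest phase. Collection continues during the study and serious AEs are listed, so such events are only outside the treatment-emergent tables. Nothing in the article shows that AEs peak after stopping.

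**Conclusion.** The point holds in a limited form and is minor: a cheap improvement, not a flaw that threatens the trial's conclusions. The direction follows from the article's own text, since tables limited to time on treatment meet a design that expects longer treatment in one arm. The size rests on exponential PFS, on PFS as a proxy for treatment time, and on AE rates that the article does not supply. The proxy is imperfect: section 2.3.3 allows alectinib to continue after oligoprogression, and treatment may also stop early for toxicity. If TDM has no effect on PFS, this particular tilt disappears. The missing post-dose period is a matter of definition, and its effect cannot be sized from the article.

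**What to change.** Keep the crude worst-grade tables and make two additions.

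1. For the by-arm tables and for the toxicity contrasts in section 2.3.4, report exposure-adjusted first-event rates, cumulative incidence of grade ≥3 AEs at a fixed time such as 12 months with treatment stop as a competing event, or preferably both. They complement each other. The rate removes the tilt when the AE rate is constant, but it averages early and late risk. The fixed-time incidence handles early AEs well but leaves part of the gap, as step 5 shows. The contrast by dose increase needs the same care, because a patient must remain on treatment long enough to receive an increase.
2. Define the treatment-emergent window to include a fixed period after the last dose, for example 30 days or until the next anticancer drug starts, so that worsening soon after stopping enters the worst grade.

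The cost is analysis-plan wording and a little more programming. The treatment-emergent definition already requires AE timing to be related to treatment dates. The downside is that some late AEs related to progression will be counted. Patient care does not change.
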